## Abstract

**Background:**

Chronic obstructive pulmonary disease (COPD) is the third cause of death worldwide. COPD is characterised by dyspnoea, limited exercise tolerance, and muscle dysfunction. Muscle dysfunction has been linked to dysregulation between muscle protein synthesis, myogenesis and degradation mechanisms. Conventional concentric cycling has been shown to improve several clinical outcomes and reduce muscle wasting in COPD patients. Eccentric cycling is a less explored exercise modality that allows higher training workloads imposing lower cardio-metabolic demand during exercise, which has shown to induce greater muscle mass and strength gains after training. Interestingly, the combination of eccentric and concentric cycling training has scarcely been explored. The molecular adaptations of skeletal muscle after exercise interventions in COPD have shown equivocal results. The mechanisms of muscle wasting in COPD and whether it can be reversed by exercise training are unclear. Therefore, this study aims two-fold: (1) to compare the effects of 12 weeks of eccentric (ECC), concentric (CONC), and combined eccentric/concentric (ECC/CONC) cycling training on muscle mass and function, cardiometabolic health, physical activity levels and quality of life in severe COPD patients; and (2) to examine the molecular adaptations regulating muscle growth after training, and whether they occur similarly in specific muscle fibres (i.e., I, IIa and IIx).

**Methods:**

Study 1 will compare the effects of 12 weeks of CONC, ECC, versus ECC/CONC training on muscle mass and function, cardiometabolic health, levels of physical activity and quality of life of severe COPD patients using a multicentre randomised trial. Study 2 will investigate the effects of these training modalities on the molecular adaptations regulating muscle protein synthesis, myogenesis and muscle degradation in a subgroup of patients from Study 1. Changes in muscle fibres morphology, protein content, genes, and microRNA expression involved in skeletal muscle growth will be analysed in specific fibre-type pools.

**Discussion:**

We aim to demonstrate that a combination of eccentric and concentric exercise could maximise the improvements in clinical outcomes and may be ideal for COPD patients. We also expect to unravel the molecular mechanisms underpinning muscle mass regulation after training in severe COPD patients.

*Trial Registry*: Deutshches Register Klinischer Studien; Trial registration: DRKS00027331; Date of registration: 12 January 2022. https://www.drks.de/drks_web/navigate.do?navigationId=trial.HTML&TRIAL_ID=DRKS00027331.

## Background

Chronic obstructive pulmonary disease (COPD) is the third leading cause of death worldwide [1, 2]. Clinically, COPD is primarily characterised by airflow limitation resulting from inflammation and remodelling of the airways associated with parenchymal destruction emphysema [3]. Consequentially, COPD impairs functional capacity, decreases mobility, and promotes sedentary behaviour (i.e., disuse) due to the progressive worsening of dyspnea [4]. In fact, the inability to be physically active is one of the frequent complaints expressed by patients with COPD, which represents a downward spiral that aggravates the systemic consequences of the disease due to disuse [5]. Furthermore, patients with COPD frequently develop metabolic and cardiac complications (i.e., insulin resistance, dyslipidaemia, hypertension, etc.), which in association with the above-mentioned clinical manifestations, results in reduced quality of life [3] and an increased mortality rate in COPD patients in comparison to their healthy counterparts [6].

A common extra-pulmonary manifestation in patients with COPD is the lower limb muscle dysfunction**,** which includes structural and morphological alterations compromising muscle function and mass, as evidenced by reduced muscle endurance and strength [7]. The reduced muscle endurance capacity in COPD patients is the result of impaired muscle oxidative capacity, a shift toward a glycolytic muscle fibre type (type II) distribution (i.e., a low fraction of type I fibres) [8], reduced capillarity (i.e., low capillary to fibre ratio) and reduced cross-sectional area (CSA) of all muscle fibre types reported in COPD [9]. These changes are clinically manifested by reduced exercise endurance capacity and increased fatigability [3], which also limit daily life activities and exacerbate poor health status in COPD [10]. The reduced muscle strength is evidenced by an accelerated decline in lower limb muscle strength in COPD compared to healthy counterparts (4% vs. 1–2% per year) [11]. The muscle strength loss has been closely associated with an involuntary muscle mass loss or muscle wasting [11], which affects 10–40% of COPD patients [12] and has been related to multiple complications such as poorer survival [13–15], and increased hospital readmission, need for mechanical ventilator support (i.e., health care resources), morbidity, and mortality [3, 16]. Furthermore, muscle wasting and dysfunction are clinically associated with decreased functional capacity (i.e., 6-min walking test; 6MWT) [17, 18], increased risk of falls (i.e., timed up and go; TUG), limited mobility and daily physical activity, which promotes sedentary behaviour, and decrease quality of life in COPD patients [19].

### Exercise in pulmonary rehabilitation for COPD

Pulmonary rehabilitation (PR) has the challenge of reversing the deleterious impact of muscle wasting and dysfunction in conjunction with other systemic manifestations of COPD (e.g., hypertension, dyslipidaemia, and diabetes). However, exercise must accommodate the limitations of these patients. These limitations result from the inability to increase oxygen delivery to the peripheral muscles, gas exchange inefficiency in the lungs, constraints on lung mechanics (i.e., dynamic hyperinflation and flow limitation), and pulmonary hypertension during exercise [20]. Several clinical trials have shown that exercise markedly improves functional performance, health-related quality of life, perception of dyspnoea, muscle mass, and exercise capacity in COPD patients [21–23]. Endurance training has probably been the most common exercise modality prescribed for patients with COPD [24–26], which has shown to improve exercise tolerance, quality of life [26], muscle oxidative capacity [27], promote a fibre-type shift from type IIx to type I fibres [28], and increase CSA of all muscle fibre types [9]. Furthermore, it enhanced mitochondrial oxidative enzyme activity and increased capillary to muscle fibre ratio in patients with COPD [27]. However, there is also evidence that aerobic training may not be ideal for COPD as it could induce excessive oxidative stress and even decrease muscle mass in these patients [29–31]. On the other hand, resistance training has shown to increase muscle mass and strength in severe COPD patients, evidencing a preserved responsiveness to increases in muscle mass and strength in these patients [32]. Furthermore, resistance training has been shown to improve functional performance, mobility, and quality of life [33]. Although it is clear that exercise can reverse some of the clinical manifestations of COPD, the ventilatory constraints and lower limb muscle weakness of these patients limit their participation in traditional exercise, which reduces the extent of the benefits obtained from exercise. Thus, a modality of exercise to maximise the benefits for these patients is still a matter of study.

### Eccentric cycling training as a potentiator of PR in COPD

Eccentric cycling is a more novel and less explored training modality, in which eccentric training of the lower limb muscles is performed when resisting the backward rotational movement of the cranks generated by an eccentric ergometer. We have recently demonstrated that eccentric cycling is safe and could be ideal for COPD patients since it imposes lesser cardiopulmonary, metabolically, and perceptually demand (i.e., lower oxygen consumption, dyspnoea, and blood pressure) and allows greater workload production for the same metabolic demand than concentric cycling in COPD patients [34]. Moreover, when eccentric cycling is used as a training modality, it has shown to induce greater gains in muscle mass and strength [35, 36], and functional performance [37] in several clinical populations and COPD [35–37]. MacMillan et al. reported that 10-week eccentric cycling training increased muscle strength and mass in moderate COPD patients [35]. In line with that, Inostroza et al. [38] showed that 12 weeks of eccentric cycling training induced increases in muscle mass of the lower limbs and functional capacity, as shown by a 25% increase in the 6-min walking test, which was accompanied by improvements in quality of life of these patients. Thus, it seems that eccentric cycling training could be an ideal exercise modality for COPD. However, a limitation of eccentric cycling training is the modest adaptation to the oxidative metabolism after training [35, 39]. Interestingly, Steiner et al. showed that concentric cycling training increased mitochondrial volume density (14%) and increased aerobic capacity in COPD. However, muscle mass was decreased by 1%, suggesting that aerobic training may not be ideal for COPD [39]. Thus, as concentric cycling training has shown to induce metabolic improvements (i.e., insulin sensitivity, lipid profile, fat-mass, and mitochondrial adaptations), and eccentric cycling has shown to improve muscle mass and functional performance after training, it seems plausible to think that a combination of ECC and CONC (ECC + CONC) training could maximise the benefits of training for COPD patients.

### Muscle wasting in COPD

It is known that the Akt/mTOR/p70s6K/rS6 signalling pathway and the expression of myogenic regulatory factors (MRFs) (e.g., Myf5, Myod, myogenin) are essential mechanisms regulating muscle growth. It is known that the maintenance of skeletal muscle mass is dependent on the balance between the rates of muscle protein synthesis and degradation. However, this balance is tilted toward reduced protein synthesis and increased protein degradation, causing muscle wasting in COPD [40–42]. Muscle wasting has been associated with elevated systemic inflammation, oxidative stress, and physical deconditioning (e.g., disuse) of COPD patients [43, 44]. Intriguingly, some unclear results exist regarding the regulation of this balance, with studies reporting a decreased muscle protein synthesis rate in COPD patients [45], while others reported an increased protein synthesis in severe COPD when compared with healthy controls [46]. Additionally, MRFs and myostatin are also increased in COPD patients [47, 48]. This apparent contradictory regulation has been proposed to be an attempt of skeletal muscle to counterbalance an increased protein degradation in COPD patients.

### MicroRNAs as potential biomarkers of muscle dysfunction in COPD

In recent years, muscle-specific microRNAs (miRs) have been pointed out as crucial muscle growth regulators during disuse, overloading, and chronic diseases since they could play a significant role in proliferation and differentiation during myogenesis [10]. Farre-Garros et al. showed that muscle miR-542-3p and miR-542-5p were associated with muscle dysfunction and could suppress muscle protein synthesis in COPD [49]. Furthermore, Barreiro et al. showed that the levels of muscle miR-1, miR-206, miR-486, miR-29b, miR-133a, miR-27a, and miR-181a were lower in COPD patients with muscle wasting [50]. Interestingly, miR-208b and miR-499 have shown to be encoded in type I fibres only [51]. Thus, it seems that microRNAs are involved in muscle mass regulation, and their expression in muscle might be fibre-type specific [52]. Similarly, plasma levels of several muscle-specific miR (miR-1, miR-499, miR-181, miR133, and miR-206) have shown to be higher in patients with severe COPD than in controls [53, 54]. Furthermore, plasma miRs (miR-21, miR-146a, miR-221, miR-222) could be associated with exercise training [54, 55]. Thus, it appears that miRs in plasma could be an excellent biomarker to monitor muscle mass function and the effects of exercise in COPD patients. However, this has not been explored.

### Effects of exercise on skeletal muscle growth and degradation in COPD

Although muscle mass and strength have shown to increase after training in patients with severe COPD [32], this increase seems to be smaller than in control individuals. This may suggest a disconnection between changes in protein expression and muscle growth in COPD patients. However, acute aerobic exercise has shown to increase muscle protein degradation in COPD [26, 56, 57]. For instance, endurance exercise training (i.e., concentric cycling) increased the ubiquitin–proteasome (UP) system after training in COPD patients [58]. Also, Vogiatzis et al. reported greater ubiquitination after 12-week endurance training, which was associated with reduced protein synthesis in severe COPD patients [26]. Barreiro et al. also reported greater oxidative stress damage to muscle proteins after endurance training in severe COPD patients [29]. Therefore, it seems that endurance training could induce protein degradation in severe patients with COPD [26, 31]. The role of exercise on muscle autophagy has not been much investigated in COPD, but its activation depends on exercise intensity, volume, and modality [59–62]. The activation of autophagy with exercise may serve to enhance the removal of damaged proteins and organelles such as mitochondria [63, 64]. Additional research is needed to establish if improved autophagy can impact muscle oxidative metabolism and protein synthesis in COPD patients. Interestingly, Valladares-Ide et al. have recently shown that protein synthesis (mTOR and p70s6K phosphorylation) and MRF expression (MyoD and MRF4) increased, and markers for protein degradation (Atrogin-1 and MuRF-1) decreased after repeated bouts of eccentric cycling in young, healthy men [65]. They concluded that repeated eccentric cycling seems to induce a muscle-signalling response leading to muscle growth with limited muscle degradation signalling. Recently, eccentric exercise showed to stimulate muscle protein synthesis and decrease autophagy in an cachectic murine model, while no changes were observed after concentric exercise [66]. Thus, it is possible that eccentric exercise training could stimulate muscle protein synthesis to a greater extent than classic interventions such as concentric endurance training interventions in COPD.

### Muscle fibre-specific adaptations

It is known that human skeletal muscle contains a mixture of fibres exhibiting different contractile and metabolic properties. In general, the slow-twitch type I fibres possess a greater capacity for oxidative energy production, whereas the fast-twitch type II fibres demonstrate a larger glycolytic and force production capacity. Although the percentage of type I fibre is decreased and type II is increased in COPD, the fibre CSA is reduced more in type II fibres of COPD patients in comparison with healthy controls [52]. It has been shown that the fibre type and morphology can be changed depending on the exercise intervention performed [23]. There is growing evidence that muscle adaptations are encoded to a specific type of muscle fibres, and it seems that molecular adaptations to exercise are fibre type-specific, which depend upon the type and intensity of the exercise, and the involvement of type I and type II fibres in such exercise. This could explain equivocal results in COPD when analysing the synthesis and degradation pathways in whole muscle. Thus, it would be interesting to investigate whether exercise training regulates the molecular pathways for muscle growth and degradation in a fibre-specific manner in COPD.

Therefore, eccentric cycling is lesser cardiorespiratory and metabolic demanding than conventional endurance concentric cycling, which allows training at much higher workloads. Furthermore, eccentric cycling training in COPD patients improves functional capacity, muscle strength and mass. On the other hand, concentric training has shown improvements in the oxidative and metabolic capacity of COPD patients. Hence, there is a possibility that when combining eccentric and concentric cycling training, the adaptations in COPD could be maximised. Furthermore, there is a lack of knowledge on changes within skeletal muscles underlying these beneficial effects induced by exercise in COPD.

## Methods

### Aim

The aim of this project is two folds. To investigate the effects of eccentric and concentric, eccentric, and concentric cycling training on (1) muscle mass, muscle function, functional performance, blood markers of cardiometabolic health, physical activity levels and quality of life in patients with severe COPD; and (2) the regulatory pathways for muscle synthesis (Akt/mTOR/p70s6K/rS6), MFR expression, muscle degradation (UP and autophagy), and miRs expression in the whole muscle and a fibre-type specific manner after training.

### Experimental design

This project will investigate the effects of combined concentric and eccentric cycling training (ECC + CONC), purely eccentric (ECC), and purely concentric cycling (CONC) training on muscle mass, muscle function, functional performance, daily physical activity level and quality of life of severe COPD patients using a multicentre randomised clinical trial design. Furthermore, the study will compare the effects of exercise training on the regulatory pathways of muscle synthesis (Akt/mTOR/p70s6K/rS6), MFRs expression and muscle degradation (UP and autophagy) in a fibre-specific manner in severe COPD patients. We will examine the differential response to exercise training in whole muscle homogenates and isolated muscle fibres (type I and II muscle fibres) from VL muscle samples taken from a subgroup of patients from each training group (ECC + CONC, ECC, and CONC). Finally, we will assess the relationship between plasma and muscle miRs expression to investigate the validity of plasma miRs as biomarkers of muscle dysfunction.

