### Clinical outcomes

#### Blood samples

Resting venous blood samples will be collected following 12-h overnight fast from the antecubital vein will be collected in two EDTA and two serum vacutainer tubes and will be centrifuged for 10 min at 5000 rpm. Glucose and insulin concentrations, lipid profile (triacylglycerols, total cholesterol, high-density lipoprotein cholesterol, low-density lipoprotein cholesterol) and C-reactive protein will be assessed. Furthermore, inflammatory markers (IL-6, IL-1β, and TNF-α) and plasma microRNAs will also be analysed.

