#### Cross-sectional area (CSA)

Magnetic resonance imaging (MRI) will be performed on both thighs after 15 min lay down rest. MRI images of both thighs will be T1 weighted. Images at 20%, 50%, and 80% distance from the patella and the anterior inferior iliac spine will be used for comparisons of the CSA of different portions of the quadriceps muscle. Whole quadriceps muscle CSA will be measured (ImageJ 1.41, NIH) [67].

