### Ethics and dissemination

Regarding the muscle biopsies, we decided to perform this procedure in a subgroup of each training group to minimise the number of patients undertaking an invasive procedure. We will ensure that all patients receive the best medical attention before, during, and after the biopsy. Before a patient is eligible for muscle biopsy, a complete medical screening will be performed to assess any risks. Furthermore, although it has been reported that complications after muscle biopsies in VL are very low and rare (0.17%, please see Refs. [81, 86]). The most frequently reported complication was local skin infection (0.06%), and in most of these cases, there was a subject error that contributed to the complication (e.g., occlusive dressing, stitch left in too long). The participant will be advised regarding post-biopsy care and given a written copy of the care instructions. The participant will be called the day following the biopsy to assess any related symptoms and generally seen within 1–3 days for the initiation or resumption of exercise training. All biological samples will be kept frozen at − 80 °C for up to 5 years, after which this will be discarded.

Findings of this study are planned to be published in peer-reviewed journals and presented in international conferences with data regarding (1) functional and physiological outcomes, (2) muscle fibber morphology changes after exercise interventions, (3) molecular markers of protein synthesis and degradation changes after interventions in COPD patients, and (4) relationship between miRs from plasma and skeletal muscle samples from COPD patients.

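### Relating plasma to muscle microRNAs cannot show that plasma microRNAs are valid markers of muscle dysfunction; they need to be related directly to quadriceps CSA and strength

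*Protocol article*

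**What the plan says.** The last sentence of Experimental design names both the analysis and the inference to be drawn from it: "we will assess the relationship between plasma and muscle miRs expression to investigate the validity of plasma miRs as biomarkers of muscle dysfunction". Ethics and dissemination lists the same analysis as its fourth publication topic: "relationship between miRs from plasma and skeletal muscle samples from COPD patients".

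The background says what the marker is for. The section on microRNAs as potential biomarkers suggests that "miRs in plasma could be an excellent biomarker to monitor muscle mass function and the effects of exercise in COPD patients", and the Background describes lower limb muscle dysfunction as "structural and morphological alterations compromising muscle function and mass, as evidenced by reduced muscle endurance and strength".

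Measures of that target are in the plan. Under Cross-sectional area, "Whole quadriceps muscle CSA will be measured" by MRI, and the MVC section measures knee extensor strength. Under Blood samples, inflammatory markers "and plasma microRNAs will also be analysed". All three sections stand under the heading Clinical outcomes. Muscle tissue comes only from the biopsy subgroup of 30 described under Molecular analyses.

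Nowhere does the article relate plasma microRNAs to CSA, MVC or any other measure of muscle mass or function.

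**The concern.** The analysis named does not test the claim attached to it. A plasma–muscle association says that blood reflects what the tissue expresses. Whether blood also reflects how much muscle a patient has, or how strong it is, is a separate question that this association does not answer.

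Two errors become possible. A plasma microRNA that agrees well with muscle could be reported as a valid marker of dysfunction with no evidence linking it to mass or strength. A plasma microRNA that does track mass or strength, but is unrelated to the level in the biopsy, could be passed over. The only data used to judge validity would also come from at most 30 patients, a number chosen for other endpoints, and patients on anti-platelet or anti-coagulation therapy are excluded from biopsy.

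**Working it through.** **1. Patients available**

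- Plasma–muscle pairs: 3 groups × 10 biopsied = 30, as stated under Molecular analyses. That size was derived from effect sizes of 1 to 2.5 for fibre type, myogenic factors and p70S6K. The stated base of 8 per group is about what a two-sided two-sample t-test needs at an effect size of 1.5 (8.06 per group; alpha 0.05, power 0.8). It was not derived for a correlation.
- Whole trial: 3 × 22 = 66 (Participants).
- With the article's 30% dropout, patients available for change analyses: 30 × 0.7 = 21 and 66 × 0.7 ≈ 46. Baseline analyses need not lose patients to dropout.

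**2. Does a plasma–muscle correlation fix the plasma–dysfunction correlation?**

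Let a be the plasma–muscle correlation and b the correlation of muscle microRNA with dysfunction. The plasma–dysfunction correlation must lie within

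a·b ± √[(1 − a²)(1 − b²)].

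The documents give neither a nor b, so these are assumed values:

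| a | b | a·b | half-width | possible range |
|---|---|---|---|---|
| 0.5 | 0.5 | 0.25 | 0.75 | -0.50 to 1.00 |
| 0.6 | 0.5 | 0.30 | √(0.64 × 0.75) = 0.69 | -0.39 to 0.99 |
| 0.7 | 0.5 | 0.35 | √(0.51 × 0.75) = 0.62 | -0.27 to 0.97 |
| 0.8 | 0.7 | 0.56 | √(0.36 × 0.51) = 0.43 | 0.13 to 0.99 |

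The sign is determined only when a² + b² exceeds 1, as in the last row (0.64 + 0.49 = 1.13). These are mathematical limits, not expected errors.

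**3. What direct analysis could gain in precision**

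Fisher z, two-sided 0.05: power = Φ(atanh(r)·√(n − 3) − 1.96). For an assumed r = 0.4, atanh(r) = 0.424.

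- n = 30: 0.424 × √27 − 1.96 = 0.24, power 0.60.
- n = 66: 0.424 × √63 − 1.96 = 1.40, power 0.92.
- For change analyses after 30% loss: 0.44 at n = 21 and 0.79 at n = 46.
- Other assumed values: r = 0.3 gives 0.36 (n = 30) and 0.69 (n = 66); r = 0.5 gives 0.81 and 0.99.

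These are single, unadjusted tests. The assay section lists 12 microRNAs, so two outcomes make 24 tests. With a Bonferroni bound (0.05/24 = 0.0021, critical value 3.08) and three covariates at n = 66: 0.424 × √60 − 3.08 = 0.20, power about 0.58. The bound is conservative. False discovery control would be expected to fall between 0.58 and 0.92.

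**The case against.** **The article is condensed, and fuller analyses may sit in an unseen plan.** True of methods in general: the Statistical analysis section describes no association analysis at all. But the article does not leave the route to validity open. It names one, and that route does not reach the stated target. This is a mismatch, not a missing detail.

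**Muscle microRNA is a reasonable intermediate.** The background reports that several muscle microRNAs "were lower in COPD patients with muscle wasting", so agreement with tissue is a sensible first step. That stands as a rationale for keeping the analysis. It does not carry the validity claim, because the association with wasting need not transfer to plasma (step 2).

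**Several stronger readings are tempting, and the documents do not support them.**

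- *That plasma microRNAs are measured in all 66 patients.* The Clinical outcomes heading suggests it. Against that, the Aim places microRNAs with the molecular objective, the whole-trial list in Experimental approach omits them, and the plasma assay is described beside the muscle assay after the biopsy section.
- *That negatively correlated markers would be rejected.* The article sets no threshold, required sign or decision rule, and a strong negative association is still a relationship.
- *That the background shows plasma and muscle levels moving in opposite directions.* Some plasma microRNAs "have shown to be higher in patients with severe COPD than in controls", but that contrast is COPD against controls, whereas the muscle contrast concerns wasting within COPD. Together they do not fix a direction among severe patients.
- *That power would rise to 0.92.* This assumes r = 0.4 for two different relationships and ignores covariates and multiplicity.

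**The aim is minor.** Biomarker validity is absent from the abstract's aims and the formal Aim, and the publication topic promises only a relationship. This limits the weight of the point without removing it.

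**Conclusion.** The point holds in a limited form. As written, the plan would draw a conclusion about muscle dysfunction from an analysis that contains no measure of muscle mass or function. Under plausible assumed correlations (0.6 and 0.5) the relationship of interest is left undetermined even in sign, from -0.39 to 0.99. This conclusion does not depend on how many patients have plasma microRNA data, nor on any power figure.

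The possible gain in precision does depend on assumptions. It exists only if plasma microRNAs are assayed beyond the biopsy subgroup. For r = 0.4 and one unadjusted test, power would go from 0.60 at n = 30 to 0.92 at n = 66, and the latter figure falls once covariates and multiplicity are handled. If only the subgroup is assayed, the direct analysis gains no patients, but it still answers the right question.

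This is a secondary aim. Nothing about the comparison of the three training groups changes.

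**What to change.** Either of two changes resolves it.

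1. **Test the claim directly (preferred).** In every patient with plasma microRNA data, regress baseline quadriceps CSA and MVC on each plasma microRNA, adjusted for age, sex and FEV1. Then regress change in CSA and MVC on change in plasma microRNA, adjusted for arm. Control the false discovery rate across the microRNAs and both outcomes. Keep the plasma–muscle relationship in the biopsy subgroup as supporting mechanistic evidence, not as the criterion of validity.
2. **Narrow the claim.** Reword the last sentence of Experimental design so that it promises only agreement between plasma and muscle microRNAs.

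In both cases, state whether plasma microRNAs are assayed in the whole trial or only in the biopsy subgroup.

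The cost is a few regressions or one reworded sentence, with no new visits or measurements in patients who already have plasma microRNA data. If only the subgroup is assayed and the sponsor wants the larger sample, PCR would be needed in up to 66 − 30 = 36 further patients.
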